## Abstract

**Background::**

Compared with open lumbar microdiscectomy, percutaneous endoscopic lumbar discectomy (PELD) has the advantages of remarkable preservation of paravertebral structures, less bleeding, shorter operation time and fewer complications, it is a common method for the treatment of lumbar disc herniation (LDH). Local anesthesia is recommended during PELD. However, intraoperative pain is sometimes difficult to control satisfactorily. The efficacy of bilateral intervertebral foramen block (IFB) for pain management in PELD remains unclear. Therefore, this regimen is utilized in a randomized controlled trial for the assessment the safety and effectiveness of bilateral IFB for PELD pain control.

**Method::**

This is a single center and randomized controlled trial which will be implemented from September 2020 to September 2021. This research protocol is in accordance with the items of the Standard Protocol for Randomized Trials, which was authorized through the Ethics Committee of Huzhou Central Hospital & Affiliated Centre Hospital of Huzhou University (HZCH0465-0864). 100 participants who undergo PELD will be analyzed. Inclusion criteria contains

The exclusion criteria contains:

Patients will be randomly divided into bilateral IFB group (with 50 patients) and local infiltration analgesia group (with 50 patients). Primary outcomes are pain score at different time points. The secondary outcomes are the operative time, radiation exposure time, length of hospital stay and postoperative complications. All the analysis is implemented through applying the IBM SPSS Statistics for Windows, version 20 (IBM Corp., Armonk, NY, USA).

**Results::**

The clinical outcome variables between groups are illustrated in the Table 1.

**Conclusion::**

This investigation can offer a reliable basis for the effectiveness and safety of IFB in treating the PELD pain.

**Trial registration::**

This study protocol is registered in Research Registry (researchregistry5985).

## Introduction

1

Lumbar disc herniation (LDH) is a familiar cause of lower extremity radiation pain and low back pain and conservative treatment can improve symptoms of most cases.^[1,2]^ About 80% of the patients suffered from sciatica caused by LDH, which imposes heavy burden on society, families, and individuals.^[3,4]^ In these cases, 10% to 20% of the patients received conservative treatment, but the pain continued, and surgery should be considered.^[5]^ Compared with open lumbar microdiscectomy, percutaneous endoscopic lumbar discectomy (PELD) has the advantages of remarkable preservation of paravertebral structures, less bleeding, shorter operation time, and fewer complications, it is a common method for the treatment of LDH.^[6,7]^

For patients with LDH undergoing surgery with spinal anesthesia or general anesthesia, it is hard to detect the accidental injury of the cauda equina nerve and nerve root due to sensory blockade.^[8]^ Although local anesthesia is recommended during PELD for avoiding nerve root injury, intraoperative pain is sometimes difficult to control satisfactorily under local anesthesia only,^[9,10]^ especially during the process of foraminoplasty, working channel insertion, and nucleus pulposus removal.

Severe pain during foraminoplasty and working channel insertion is considered to originate from the posterior longitudinal ligament. A local intervertebral foramen block (IFB) can block homolateral sinuvertebra nerve and spinal nerve located in the neuroforamen. Our preliminary research has indicated that IFB was associated with improved outcomes in terms of postoperative pain and opioid consumption. However, due to the small sample size and poor study design, the efficacy of bilateral IFB for pain management in PELD remains unclear. Therefore, this regimen is utilized in a randomized controlled trial for the assessment the safety and effectiveness of bilateral IFB for PELD pain control. We assume that that IFB is effective and safety in reducing postoperative pain in PELD.

## Methods

2

### Study design

2.1

This is a randomized controlled, single center trial which will be implemented from September 2020 to September 2021. This research protocol is in accordance with the items of the Standard Protocol for Randomized Trials, which was authorized through the Ethics Committee of Huzhou Central Hospital & Affiliated Centre Hospital of Huzhou University (HZCH0465–0864), and it has been registered in the research registry (researchregistry5985). All patients had signed consent forms before the surgery.

### Population and randomization

2.2

100 participants who undergo PELD will be analyzed. In the random envelope, all patients are assigned a random number via using the random number (Table 1), and the result of allocation are hidden. Patients will be randomly divided into bilateral IFB group (with 50 patients) and local infiltration analgesia group (with 50 patients). Inclusion criteria contains

1.patients diagnosed with LDH undergoing PELD;2.people between the ages of 18 and 75;3.consistent imaging evidence of herniation at a same level (CT or MRI);4.receive conservative treatment for 2 months.

**Table 1 T1:**
[figure not shown]
Comparison of follow-up outcomes among two groups.

The exclusion criteria contains:

1.patients with the history of severe renal and hepatic dysfunction;2.more than one responsible level3.LDH combined with other spinal diseases needing advanced surgical treatment (such as fracture, spondylolisthesis, lumbar spinal stenosis, tumor, etc.);4.Patients have mental illness that will prevent their willingness to participate in the study.

### Intervention

2.3

#### Local anesthesia group

2.3.1

Patients receive the surgeries in prone position on the radiolucent Table 1. After 2 to 3 ml of 0.3% ropivacaine is infiltrated into the local skin, the selected skin entry point is pierced with an 18-gauge needle, and the track is anesthetized with 8 to 10 ml of 0.3% ropivacaine. The facet joint is anesthetized with 3 to 5 ml of 0.3% ropivacaine when the needle arrives at SAP. The following surgical procedures, such as removal of nucleus pulposus, insertion of working channel, and foraminoplasty, are the same as the procedures of conventional PELD.

#### Bilateral IFB group

2.3.2

In case of lateral and anteroposterior fluoroscopy, 18-gauge is inserted into contralateral monosegmental intervertebral foramen. 2.5 ml of 0.3% ropivacaine is infiltrated into the contralateral intervertebral foramen for the free anesthesia. Subsequently, patients receive the traditional local anesthesia with 0.3% ropivacaine, which is the same as those of the local anesthesia group for SAP anesthesia, trajectory and homolateral skin. Then adjust the needle the homolateral monosegmental intervertebral foramen. A total of 2.5 ml of the 0.3% ropivacaine is infiltrated into the homolateral intervertebral foramen to conduct the sensory-motor dissociation anesthesia. The following surgical procedures is the same as the procedures of conventional PELD.

### Outcome measures

2.4

Primary outcomes are pain score at different time point. Visual analog scale (VAS) is used to assess the pain (10: the maximum possible pain and 0: absent pain).^[11]^ The secondary outcomes are the operative time, radiation exposure time, length of hospital stay, and postoperative complications. The radiation exposure time is obtained from the G-arm computer at the end of each procedure. Oswestry Disability Index (ODI)^[12]^ is also recorded at 7 days, 12 weeks, and 1 year postoperatively.

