### Statistical analysis

2.5

All data are recorded into the Microsoft Excel 2010, and then they are analyzed via applying the IBM SPSS Statistics for Windows, version 20 (IBM Corp., Armonk, NY, USA). Afterwards, all the data are expressed with appropriate characteristics such as mean, median, standard deviation as well as percentage. Continuous and categorical variables are analyzed using χ^2^-tests and independent *t* tests, respectively. Intention-to-treat analysis is used for the outcome assessments. When *P* value <.05, it is considered to be significant in statistics.

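### Pain at several unnamed time points is the primary outcome, none is designated as deciding, and the only threshold is an unadjusted P<.05

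*Protocol article*

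**What the plan says.** Section 2.4 (Outcome measures) states "Primary outcomes are pain score at different time point", and the Method part of the abstract repeats it: "Primary outcomes are pain score at different time points". Pain is scored on a 0 to 10 VAS. The only assessment times in the text (day 7, week 12 and one year) are attached to the Oswestry index, not to the VAS.

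Section 2.5 (Statistical analysis) has one sentence on tests, beginning "Continuous and categorical variables are analyzed using" and naming chi-square and independent t tests. Its threshold is "When *P* value <.05, it is considered to be significant in statistics". It gives no adjustment, order of testing, joint model or success rule.

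The pain period is not settled either. The Introduction's hypothesis is that "IFB is effective and safety in reducing postoperative pain in PELD". The rationale in the same section, and the recommendation in the Discussion, concern pain during the operation.

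**The concern.** A primary outcome should identify the comparison on which the trial is judged. Here several pain scores share that status, and nothing in the text ranks or combines them. A reader applying section 2.5 as written would run one two-group test per time point and call each result below .05 significant.

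Two things are then at stake. First, the error rate of the claim that the block reduces pain is not fixed at 5%. Second, both the period and the time point that carry the claim could be chosen after the results are seen, and any choice would fit the text. The article's Conclusion expects the trial to provide a dependable basis for judging effectiveness, and that judgement rests on this outcome.

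**Working it through.** **Inputs from the article**
- Threshold: .05 (section 2.5). Sidedness is not stated; two-sided is assumed.
- Size: "100 participants who undergo PELD will be analyzed", 50 per arm (section 2.2). A t test then has 50 + 50 − 2 = 98 degrees of freedom, so a normal approximation is adequate.
- Number of VAS time points, k: not in the visible text. Values of 2, 3, 5 and 7 are assumed.
- Correlation between the test statistics at different times, ρ: not given. Values from 0 to 0.9 are assumed, equal for all pairs.
- Success rule: not given. The calculation takes the any-one rule, under which one significant time point suffices.

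**Plan's own figure.** With a single test (k = 1), the error is 1 − 0.95 = 5%, which agrees with the threshold. There is no sample-size calculation to reproduce: no target difference, standard deviation or power is given.

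**Independent tests (ρ = 0).** The chance of at least one false positive is 1 − 0.95^k:
- k = 2: 1 − 0.9025 = 9.75%
- k = 3: 1 − 0.8574 = 14.3%
- k = 5: 1 − 0.7738 = 22.6%
- k = 7: 1 − 0.6983 = 30.2%

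**Correlated tests.** With c = 1.96, the chance is

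1 − ∫ φ(u) · [Φ((c − √ρ·u)/√(1−ρ)) − Φ((−c − √ρ·u)/√(1−ρ))]^k du

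| k | ρ = 0 | ρ = 0.5 | ρ = 0.7 | ρ = 0.9 |
|---|---|---|---|---|
| 2 | 9.75% | 9.1% | 8.4% | 7.0% |
| 3 | 14.3% | 12.5% | 10.9% | 8.4% |
| 5 | 22.6% | 18.3% | 14.8% | 10.2% |
| 7 | 30.2% | 23.0% | 17.8% | 11.4% |

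Divided by 5%, the table runs from 7.04/5 = 1.4 (k = 2, ρ = 0.9) to 30.17/5 = 6.0 (k = 7, ρ = 0).

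**Other success rule.** If every time point had to be significant, the chance of a false claim could not exceed that of any one test, 5%. The inflation therefore depends on the any-one rule.

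**After a fix.** One named contrast at .05 has an error of 5.0%. Splitting the level equally over k independent tests gives 1 − (1 − .05/k)^k, which is 4.92% for k = 3 and 4.90% for k = 5. Holm likewise keeps the familywise rate at or below 5%.

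**The case against.** The strongest reply is that this is a condensed article. The content of Table 1, where the Results section sends the reader for the outcome variables, cannot be seen and may list the VAS times. Multiplicity rules and repeated-measures models are commonly left to an analysis plan. Section 2.5 is a general paragraph that never says how repeated VAS scores are handled.

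Much of this stands. The absence of a multiplicity method or a mixed model is not in itself a fault of this article. What remains is that the text calls several scores primary and designates none. Naming the primary outcome is the protocol's job, and a table listing the times would still not say which one decides.

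Three stronger readings are tempting, and the documents do not support them:
- A reader might infer that the error rate is two to six times the nominal 5%. The article gives neither the number of time points nor the correlation. Six times needs seven time points and no correlation, although repeated scores from the same patient are normally positively correlated.
- A reader might infer that the plan lets any single significant time point establish efficacy. It states no success rule. It only fails to exclude that one.
- A reader might infer that separate t tests are invalid because scores within a patient are correlated. A test at one time point compares independent patients and remains valid. A joint model is a choice about efficiency, and positive correlation lowers the familywise error.

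**Conclusion.** The point holds in a limited form. The primary outcome is fixed badly: plural, with no deciding time point or summary in the text, and with only an unadjusted .05 beside it. If any one time point can carry the claim, the false-positive chance exceeds 5% for two or more time points unless the tests are perfectly correlated. Illustrative sizes are 11% to 14% for three time points and 15% to 23% for five, with correlation from 0.7 down to 0. Across two to seven time points and correlations from 0 to 0.9, the multiple is about 1.4 to 6. These figures rest on an assumed number of time points, correlation and success rule, and describe what the text permits, not what the trial will do. The open choice of the deciding time point needs no such assumption: it follows from the wording of section 2.4.

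**What to change.** 1. Reconcile the Introduction's hypothesis (postoperative pain) with its rationale and the Discussion (intraoperative pain), and state which period the primary question concerns.
2. Before any between-group comparison, name one primary contrast, tested at two-sided .05, from VAS measurements already scheduled. It can be one named time point, or the average treatment effect over the scheduled time points of that period from one repeated-measures mixed model.
3. Make the other time points secondary: tested with Holm or in a fixed order, or reported as differences with 95% confidence intervals and no claim of significance.
4. Alternatively, keep all time points primary and apply Holm. The smallest P value then has to meet .05/k, for example .05/3 = .0167 with three time points.

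The cost is a change of wording in the protocol, the analysis plan and the registry entry, plus a little analysis. No new data are needed as long as the contrast uses scores already scheduled. The visible text schedules no VAS at particular surgical steps, so a contrast built on those steps could need extra assessments. The downside for the sponsor is that an isolated significant time point can no longer carry the efficacy claim.

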## Discussion

4

To the best of our knowledge, this is the first randomized controlled trial to assess the safety and effectiveness of bilateral IFB for PELD pain control. LDH is a common orthopedic disease and a worldwide health problem characterized by low-back and radiating pain.^[13,14]^ PTED has become one of the optimal clinical treatments for LDH due to the advantages of minimal invasion, less blood loss, and rapid recovery.^[15,16]^ Surgery and anesthesia are associated with a stress reaction, immunosuppression, and postoperative pain, which prolong hospital stays and increase the economic burden of patients.^[9]^ Appropriate anesthesia is important to achieve improved clinical outcomes.^[17]^ The lack of a definitive “gold standard” and various programs of anesthesia method during operation indicate that there is much room for improving the perioperative pain control. Recently, IFB is popular used in PELD. However, if conducted unilateral IFB only, satisfactory and instant distribution of local anesthetic to the opposite side usually could not be obtained, due to the mass effect of herniated nucleus pulposus, spinal stenosis, intraspinal adhesion, different puncture site and other factors. Therefore, bilateral IFB is recommend for intraoperative pain management in PELD. Considering that the sample size is small. Our findings must be replicated in more research centers and in larger samples, and evaluate over longer periods of follow-up, before final conclusions can be drawn.

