## Conclusion

5

This investigation can offer a reliable basis for the effectiveness and safety of IFB in treating the PELD pain.

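### Safety is promised, but the only named adverse-event outcome is worded as postoperative and, with 50 patients per arm, cannot support that promise

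*Protocol article*

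**What the plan says.** Safety appears in three places in the protocol article.

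- **Aim (Introduction):** "assessment the safety and effectiveness of bilateral IFB for PELD pain control".
- **Hypothesis (Introduction):** "We assume that that IFB is effective and safety in reducing postoperative pain in PELD".
- **Conclusion (section 5, repeated in the Abstract):** "This investigation can offer a reliable basis for the effectiveness and safety of IFB in treating the PELD pain".

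The outcomes are in section 2.4. Pain score is primary, and then: "The secondary outcomes are the operative time, radiation exposure time, length of hospital stay, and postoperative complications". The Oswestry Disability Index is also recorded at 7 days, 12 weeks and 1 year. No other adverse-event outcome is named.

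The size is in section 2.2: "Patients will be randomly divided into bilateral IFB group (with 50 patients) and local infiltration analgesia group (with 50 patients".

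The Introduction says of surgery under spinal or general anaesthesia that "it is hard to detect the accidental injury of the cauda equina nerve and nerve root due to sensory blockade". It gives avoidance of nerve root injury as the reason for preferring local anaesthesia, and says that the foramen block reaches the spinal nerve. Section 2.3.2 adds 2.5 ml of 0.3% ropivacaine in the foramen on each side to the local anaesthesia that both arms receive.

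The Discussion calls the sample small and says: "Our findings must be replicated in more research centers and in larger samples", before final conclusions are drawn.

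**The concern.** If safety is part of the aim, the adverse-event outcome has to cover the events that the tested procedure could plausibly cause, and the data have to be precise enough for the statement made at the end. Both are in doubt.

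First, the arms differ by an injection into each foramen. Events tied to that difference could occur during surgery and resolve before it ends: a motor block, nerve irritation, or a reaction to the local anaesthetic. An outcome worded as postoperative complications does not include them, so the arms could differ in such events without the trial's outcome showing it.

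Second, 50 patients per arm say little about uncommon harms. A complication comparison would often be non-significant even if the risk had risen several-fold, yet the Conclusion promises a firm basis for safety while the Discussion withholds final conclusions from the same 100 patients.

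**Working it through.** **Inputs.** 50 patients per arm (section 2.2). Significance at P < .05 (section 2.5; sidedness is not stated, so two-sided is assumed). The article gives no complication rate, power or safety margin, so every event rate below is an assumption and is shown as a range. There is no stated power calculation to reproduce.

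**1. What zero or one event in the block arm would show.** This step needs no assumed rate.
- Zero events in 50, exact two-sided 95% upper limit: 1 − 0.025^(1/50) = 0.071, or 7.1%. The one-sided 95% limit is 1 − 0.05^(1/50) = 0.058, or 5.8%.
- One event in 50, Clopper-Pearson two-sided upper limit: the 0.975 quantile of Beta(2, 49) = 0.106, or 10.6%.

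**2. Chance of seeing no event at all in the block arm,** (1 − p)^50.
- True risk 1%: 0.99^50 = 0.605.
- True risk 2%: 0.98^50 = 0.364.
- True risk 5%: 0.95^50 = 0.077.

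**3. Power to detect a difference, 50 per arm, two-sided 0.05.** Section 2.5 names the chi-square test (its two data types appear transposed; the test is read here as meant for categorical data). Fisher's test is shown beside it because counts would be sparse. Both columns come from summing the binomial probabilities of every rejecting table.

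| Control vs block (assumed) | Chi-square | Fisher |
|---|---|---|
| 1% vs 5% | 0.149 | 0.024 |
| 2% vs 4% | 0.054 | 0.006 |
| 2% vs 10% | 0.383 | 0.190 |
| 5% vs 10% | 0.145 | 0.063 |
| 5% vs 15% | 0.393 | 0.244 |
| 10% vs 20% | 0.303 | 0.195 |

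Normal-approximation check for 2% vs 10%: the pooled rate is 0.06, so the power is Φ[(0.08 × √50 − 1.96 × √(2 × 0.06 × 0.94)) / √(0.02 × 0.98 + 0.10 × 0.90)] = Φ[(0.566 − 0.658) / 0.331] = Φ(−0.28) = 0.39. This agrees with the exact chi-square figure.

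By the same approximation, 80% power would need a block-arm rate of about 17% against 1% in controls, 19% against 2%, 25% against 5%, or 33% against 10%.

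**4. Width of the interval if the arms were equal.** With 2/50 in each arm (an illustration), the Newcombe 95% interval for the risk difference runs from −9.9 to +9.9 percentage points.

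**5. The passages side by side.** The Discussion says that the sample is small and that replication must come before final conclusions. The Conclusion, on the same sample, promises a reliable basis for safety. Steps 1 to 4 support the Discussion.

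**The case against.** The strongest case on the other side has five parts.

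- **The neural risk is not stated of this block.** The Introduction raises masked nerve injury for spinal and general anaesthesia, as the reason to prefer local anaesthesia. A reader might infer that the protocol identifies this as a hazard of the foramen block and then leaves it out. The text does not say so, and section 2.3.2 describes the homolateral injection as aiming at sensory-motor dissociation. This objection stands: applying the concern to the block is an inference, though one that rests on the article's own account of what the block reaches.
- **Nerve injury may be counted.** A reader might also infer that nerve injury is not recorded at all. That goes too far. An injury that leaves a deficit could be recorded as a postoperative complication, the disability index would reflect lasting functional harm, and Table 1 (not visible) or the full protocol may list events. The absence of a detailed definition from a condensed article is not held against the plan. What remains is the stated time boundary, which does not cover events confined to the operation.
- **Complications are not the only safety-related measure.** Radiation exposure time also bears on safety, because the block arm adds a fluoroscopy-guided puncture. This is correct. It is an exposure and not an adverse event.
- **Low power for rare harms is common in trials of this size.** True, and it would be no criticism if the Conclusion did not promise reliable safety evidence.
- **No passage plans to infer safety from a non-significant test.** Also true. That reading is a risk left open by the Conclusion's wording and not a stated method.

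**Conclusion.** The point holds as a modest, inexpensive improvement. Safety is part of the aim and the Conclusion, but the only named adverse-event outcome excludes, by its wording, intraoperative and transient block-related events in a trial where the tested difference is an added injection on both sides.

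With 50 per arm, even a clean result in the block arm leaves a true risk of up to 7.1% open, and a single event leaves 10.6%. These limits follow from the sample size alone. The power figures (about 38% by chi-square and 19% by Fisher for 2% vs 10%) rest on assumed rates. Across the range shown, power stays below 40%.

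The Conclusion's safety statement is therefore stronger than the design can bear, and it conflicts with the Discussion. The documents do not support the stronger claims that the protocol itself names masked nerve injury as a risk of the block, or that such injuries will go unrecorded. The efficacy comparison is not affected.

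**What to change.** 1. In section 2.4, rename the outcome as intraoperative and postoperative complications. Name at least new motor or sensory deficit, nerve-root or dural injury, and local-anaesthetic reactions. Count from the first needle through the existing follow-up. Stopping at discharge could shorten the present outcome, which states no such cut-off.
2. In section 2.5, state that complications will be reported as the risk difference between arms with its 95% confidence interval, and that a non-significant difference will not be read as evidence of safety.
3. In the Abstract and section 5, describe the safety results as preliminary and descriptive, in line with the Discussion, and quote the upper confidence limit actually observed. The 7.1% figure applies only if no event occurs.

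The cost is a few more lines on the case report form and a more modest safety statement. No extra patients or visits and no change to treatment are needed.

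### ODI is scheduled only after surgery and the named test uses no baseline, so precision for VAS and ODI may be lost, by an amount that depends on a correlation the article does not give

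*Protocol article*

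**What the plan says.** The Outcome measures section (2.4) makes pain on a 0 to 10 VAS the primary outcome: "Primary outcomes are pain score at different time point". The times are not named, so a preoperative VAS is neither stated nor excluded. For ODI the times are named: it "is also recorded at 7 days, 12 weeks, and 1 year postoperatively". No preoperative ODI is listed.

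The Statistical analysis section (2.5) states: "Continuous and categorical variables are analyzed using χ^2^-tests and independent *t* tests, respectively". The two tests are attached to the wrong variable types. With that corrected, VAS and ODI are compared by independent t test. No covariate, change score or model is mentioned.

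The Population and randomization section (2.2) fixes the size: "100 participants who undergo PELD will be analyzed", with 50 in each arm. The allocation is described without stratification.

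**The concern.** Patients enter with symptomatic disc herniation after two months of conservative treatment, so they may differ in pain and disability before surgery. If those differences carry over into the postoperative scores, part of the spread within each arm could be explained by the baseline value. A two-group t test leaves that part in the error term.

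Three things are at stake. The VAS comparison, which is the primary one, may be less precise than the same 100 patients allow. Without a preoperative ODI, a chance difference in disability between the arms can be neither seen nor adjusted for, and change in disability cannot be reported. And the two gaps differ in kind: an analysis sentence can be rewritten later, but a preoperative ODI that was never taken cannot be recovered.

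The article's own Discussion describes the sample as small, so a gain in precision that needs no extra recruitment is worth having.

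**Working it through.** **Inputs from the article.** 50 per arm (section 2.2); significance at P below .05 (section 2.5), taken here as two-sided because the side is not stated. The article gives no power, effect size, SD or correlation, so there is no figure of its own to reproduce.

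**Input assumed.** r, the correlation between baseline and outcome within an arm, is varied from 0 to 0.7.

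**Step 1: detectable difference without adjustment, 80% power.** Normal approximation: (1.960 + 0.842) × √(2/50) = 2.802 × 0.200 = 0.560 SD. With the t distribution on 98 degrees of freedom it is 0.566 SD, which is used below.

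**Step 2: effect of adjustment.** ANCOVA multiplies the residual variance by 1 − r². It follows that:
- equivalent number per arm = 50 / (1 − r²)
- equivalent extra patients = 1/(1 − r²) − 1
- detectable difference = 0.566 × √(1 − r²)

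| r (assumed) | 1 − r² | Equivalent n per arm | Extra patients | Detectable difference (SD) |
|---|---|---|---|---|
| 0 | 1.00 | 50.0 | 0% | 0.57 |
| 0.1 | 0.99 | 50.5 | 1.0% | 0.56 |
| 0.2 | 0.96 | 52.1 | 4.2% | 0.55 |
| 0.3 | 0.91 | 54.9 | 9.9% | 0.54 |
| 0.5 | 0.75 | 66.7 | 33.3% | 0.49 |
| 0.7 | 0.51 | 98.0 | 96.1% | 0.40 |

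**Step 3: price of estimating the slope.** Estimating the slope inflates the variance by about (N − 3)/(N − 4) = 97/96, or 1%. The gain becomes 1/[(1 − r²) × 97/96] − 1. That is 8.8% at r = 0.3, 32.0% at r = 0.5 and 94.1% at r = 0.7. At r = 0.2 it is 3.1%, at r = 0.1 about nil, and at r = 0 a loss of about 1%.

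**Step 4: the same gain as power.** For a true difference of 0.56 SD (80% power unadjusted, normal approximation), adjusted power is 83.6%, 89.9% and 97.5% at r = 0.3, 0.5 and 0.7.

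**Step 5: which outcomes.** Section 2.4 states: "The secondary outcomes are the operative time, radiation exposure time, length of hospital stay, and postoperative complications". None of these has a baseline value of itself, so the table applies only to VAS and ODI.

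**The case against.** The strongest reply is that this is a matter of efficiency which a condensed article may leave to a full protocol or analysis plan. Covariate adjustment is often specified there, and listing follow-up times does not prove that no baseline was planned. ODI is only described as also recorded; it is not among the listed primary or secondary outcomes. This lowers the weight of the point but does not remove it. The article is not silent here: it names its test and it names the ODI times, and both can be judged as stated.

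A reader might go further than the text allows in three ways, and the objection is right on each.

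- **That a fixed amount of precision, such as 10% to 96%, is given up.** The article gives no r. That range is simply r = 0.3 to 0.7, and 10% is not a floor. The Introduction ties intraoperative pain to foraminoplasty, working channel insertion and nucleus pulposus removal; nothing shows that pain of this kind follows preoperative pain closely.
- **That baseline pain is not recorded.** The VAS times are left open and the content of Table 1 is not available. One can say only that the named test would not use a baseline VAS.
- **That the comparison is biased by chance imbalance.** Under randomisation the t test is unbiased, and its standard error already allows for such imbalance.

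**Conclusion.** The point holds as a possible loss of precision in VAS and ODI, not as a fault of validity. As written, a baseline ODI cannot be used because none is scheduled, and a baseline VAS would not be used because the named test has no place for it.

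The size rests wholly on the assumed r: about 10%, 33% or 96% more patients at 0.3, 0.5 or 0.7, only 1% to 4% at 0.1 to 0.2, and a cost of about 1% at zero. The calculation also assumes a two-sided 5% level, complete data on 50 per arm, and a linear relation with the same slope in both arms. ANCOVA is still the better choice, since the most it is likely to cost is about 1% and the possible gain is large.

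**What to change.** In section 2.4, add one assessment of ODI and of the pain VAS before randomisation. If both are already collected, say so; then only the analysis sentence changes.

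In section 2.5, correct the pairing of tests and variable types. For VAS and ODI, replace the independent t test with ANCOVA at each postoperative time, with treatment arm as factor and the preoperative value of the same scale as covariate. The comparisons of operative time, radiation exposure time, hospital stay and complications are not affected by this point.

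The cost is one short preoperative questionnaire per patient and a revised sentence. The baseline has to be in place before patients are treated, since it cannot be obtained afterwards.
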